### Confidentiality {27}

The trial staff ensure that the participants’ anonymity is protected as far as possible. The trial complies with GCP and established practice which requires data to be anonymised as soon as it is practical to do so. Audio and video recordings are stored on a secure server with very limited access (to senior research team members and researchers working directly with a particular participant or directly involved in coding data). Participants are informed that audio-visual recordings will not be used outside of the team of researchers, and this is outlined in the consent form. Following the completion of the trial, the data will be downloaded and de-identified.

### Plans for collection, laboratory evaluation and storage of biological specimens for genetic or molecular analysis in this trial/future use {33}

Not applicable, no biological samples are collected.

### Statistical methods

#### Statistical methods for primary and secondary outcomes {20a}

The primary inference will be based on the BSID-III cognitive score at 24 months and the EPDS at 12 months. For the primary outcomes and other continuous outcomes, the mean (SD) will be presented by the allocation group, and the mean difference (plus 95% confidence interval) will be estimated using mixed-effects linear regression. For binary outcomes, the number and percentage with the outcome will be presented by the allocation group, and the risk ratio (plus 95% confidence interval) will be estimated using a mixed-effect binomial or Poisson regression model.

The unit of randomisation is a geospatial cluster as outcomes are collected at the individual level, hence the unit of analysis is the mother and the infant. There is also an additional level of clustering by the counsellor delivering the intervention. The lack of independence amongst individuals in the same cluster and standard methods of analysis will underestimate the standard error of the treatment difference yielding *p* values that are too small. To account for the correlation of outcomes within clusters, the geospatial cluster and counsellor identifier will be fitted as random effects, with counsellor nested within the geospatial cluster. The intra-class correlation coefficients for geospatial cluster and counsellor will be estimated.

For the EPDS and the GAD-7, a repeated measures model will be fitted, including the baseline, end of pregnancy and 12-month and 24-month scores. For the cognitive and emotional stimulation at home outcomes, a repeated measures model will be fitted including the 12- and 24-month scores. Mixed-effects models with maximum-likelihood estimation allow participants with incomplete repeated measures data to be included in the model, contributing to the estimation of model parameters. The mean scores with 95% confidence intervals will be plotted over time by the allocation group.

In addition to adjusting for important baseline differences between randomised groups, any differences between participants followed up to 24 months and those lost to follow-up will be adjusted for in the final models. Both unadjusted and adjusted models will be fitted, but the primary inference will be based on the adjusted model which provides unbiased estimates if the outcome data is missing at random (i.e. only dependent on observed characteristics).

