##### Secondary outcomes

The 10 secondary outcomes and the associated measures are summarised in Table 2 and Table 3.

**Table 2 Tab2:** Secondary outcomes

	Domain	Measure	Metric	Method of aggregation	Timepoint
1	Maternal depression	Edinburgh Postnatal Depression Scale (EPDS), total score	Mean difference	Mean and SD	End of pregnancy; 24 months postnatal
2	Maternal anxiety	Generalized Anxiety Disorder 7-item (GAD-7) scale, total score	Mean difference	Mean and SD	End of pregnancy, 24 months postnatal
3	Maternal antiretroviral treatment adherence	Viral Suppression (Yes/No)	Risk ratio	Frequency and percentage	End of pregnancy; 12 weeks, 12 months, 24 months postnatal
4	Exclusive breastfeeding	Exclusive breastfeeding at 6 months (Yes/No)	Risk ratio	Frequency and percentage	6 months postnatal
5	Adherence to infant immunisation schedule over the 24-month postnatal period	No. of immunisations recorded	Mean difference	Mean and SD	12 weeks, 12 months, 24 months postnatal
6	Infant diarrhoea	Any maternal report of diarrhoea over the previous 14 days.	Risk ratio	Frequency and percentage	12 weeks, 6 months, 12 months, 24 months postnatal
7	Cognitive and emotional stimulation within the home environment	Early Childhood Development section of Multiple Indicator Cluster Surveys (MICS6) Questionnaire for cognitive and emotional stimulation for children under five, total score	Mean difference	Mean and SD	12 months, 24 months postnatal
8	Infant behaviour	Parenting Stress Index, Short Form (PSI/SF: parent-child dysfunctional interaction subscale and difficult child subscale, total score	Mean difference	Mean and SD	12 months postnatal
		Externalising subscale of Child Behaviour Checklist (CBCL), total score	Mean difference	Mean and SD	24 months postnatal
9	Child language development	Language subscale of the Bayley Scales of Infant and Toddler Development III (BSID-III), Composite score	Mean difference	Mean and SD	24 months postnatal
10	Child growth (infant height and weight at 24 months)	Road to Health Book, study Weight and height measurements	Mean difference	Mean and SD	24 months postnatal

**Table 3 Tab3:** Mediators, including measures and timepoints

Mediators	Measure	
Family, relationship support and conflict	Relationship conflict questions adapted from the Romantic Partner Conflict Scale [59]. Support questions used from social support measure previously validated in South Africa [60].	Baseline, end of pregnancy, 12 weeks, 12 and 24 months

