#### Sample size {14}

The first primary outcome is the cognitive subscale on the BSID-III at 24 months of age. To achieve power of over 90% (two-sided *t*-test with a significance level of 0.05), and assuming an estimated difference of 6 points (SD 15), a total sample size of 396 women (198 per arm) is required. This calculation takes into account geospatial clustering (28 clusters per arm with an intra-cluster correlation coefficient (ICC) of 0.05) and ‘counsellor effect’ in the intervention arm (4 lay counsellors with an ICC of 0.05). To take account of attrition of up to 25%, a total sample size of 528 women is being recruited (264 per arm, 48–60 geospatial clusters, 9–11 women per cluster).

Using the EPDS assessment with a standard deviation of 5, with the same assumptions of clustering as above, a difference of 2 points between trial arms (not adjusting for baseline or repeated measurements) could be detected with 90% power and a 5% two-sided significance level. Analysis using repeated measures, taking into account within-participant correlation over time, would allow smaller differences to be detected with the same power

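### The Poisson option for risk ratios gives confidence intervals that are too wide for common binary secondary outcomes, unless robust standard errors are used

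*Protocol article*

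**What the plan says.** The protocol article, under *Statistical methods for primary and secondary outcomes {20a}*, states that for binary outcomes "the risk ratio (plus 95% confidence interval) will be estimated using a mixed-effect binomial or Poisson regression model". It gives no rule for choosing between the two models and does not say whether standard errors are model-based or robust.

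The same section describes one device for dealing with variance: "the geospatial cluster and counsellor identifier will be fitted as random effects, with counsellor nested within the geospatial cluster". Its stated purpose is to prevent standard errors that are too small. The opposite error is not considered.

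Table 2 (*Secondary outcomes*) assigns a risk ratio to three yes/no outcomes: viral suppression at four timepoints, exclusive breastfeeding at 6 months, and infant diarrhoea ("Any maternal report of diarrhoea over the previous 14 days"). No expected proportion is given for any of them. Both primary outcomes are continuous and use linear models.

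**The concern.** A Poisson likelihood ties the variance to the mean. For a 0/1 outcome with risk p it assumes variance p, while the true variance is p(1−p). When p is small the two nearly agree. When p is large they do not, and the model sees data that vary less than it allows.

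The planned random effects cannot repair this. A random intercept can add variance to the Poisson model but cannot take any away. With a common outcome its estimated variance falls to zero, and the model-based standard error stays too large.

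The outcome most exposed is viral suppression, the trial's measure of ART adherence. *Recruitment strategy* restricts entry to women already started on ART, so a high proportion suppressed is plausible, although the article gives no figure. With over-wide intervals, a real benefit could be read as no evidence of a difference.

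**Working it through.** The article states no standard error, power or interval width for a binary outcome, so there is no figure of its own to reproduce.

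**Inputs from *Sample size {14}***
- Clusters: "28 clusters per arm with an intra-cluster correlation coefficient (ICC) of 0.05". This ICC is stated for the BSID-III calculation; applying it to binary outcomes is an assumption.
- Analysable women: 198 per arm, so 198/28 = 7.07 per cluster.
- The counsellor effect ("4 lay counsellors with an ICC of 0.05") is ignored here.

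**Assumed:** the prevalence p, because the article gives none.

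**Formula.** With equal risk p in both arms and n women per arm:
- model-based Poisson variance of the log risk ratio: 2/(np)
- true variance: DEFF × 2(1−p)/(np)
- DEFF = 1 + (7.07 − 1) × 0.05 = 1.304
- ratio of standard errors: 1/√[(1−p) × DEFF]

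The formula applies while (1−p) × DEFF is below 1, that is for p above 1 − 1/1.304 = 0.23. Below that the random effect has extra variation to absorb and the ratio is about 1.

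**Check by simulation.** Beta-binomial data were generated in 56 clusters of 7 with ICC 0.05. A random-intercept Poisson model with model-based standard errors was fitted, 300 runs per setting.

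| p (assumed) | Ratio, clustering ignored: 1/√(1−p) | Ratio with DEFF 1.304 | Simulated ratio | Simulated coverage of 95% CI |
|---|---|---|---|---|
| 0.15 | 1.08 | about 1 | 0.98 | 94.7% |
| 0.30 | 1.20 | 1.05 | 1.02 | 94.7% |
| 0.50 | 1.41 | 1.24 | 1.17 | 98.0% |
| 0.70 | 1.83 | 1.60 | 1.59 | 99.7% |
| 0.80 | 2.24 | 1.96 | 2.07 | 100% |
| 0.90 | 3.16 | 2.77 | 2.71 | 100% |

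The median estimated random-effect SD was about 0 at every p of 0.30 or more. This confirms that the random effects do not correct the problem.

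**Effect on power, 80% v 90% (assumed), 198 per arm**
- log(0.90/0.80) = 0.1178
- True variance: 1.304 × [0.2/(198 × 0.8) + 0.1/(198 × 0.9)] = 1.304 × 0.001824 = 0.002378, so SE = 0.0488
- Model-based Poisson variance: 1/(198 × 0.8) + 1/(198 × 0.9) = 0.01192, so SE = 0.1092
- Power with the correct SE: Φ(0.1178/0.0488 − 1.96) = Φ(0.46), about 68%
- Power with the Poisson SE: the estimate must exceed 1.96 × 0.1092 = 0.2140, so power is Φ((0.1178 − 0.2140)/0.0488) = Φ(−1.97), about 2%

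The same steps give 59% falling to 23% for 60% v 72%, and 73% falling to 59% for 40% v 55%.

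**The case against.** The strongest objection is that the fault is inferred from silence. The article never says model-based standard errors. A condensed protocol commonly leaves the variance estimator to the SAP, which is not shown and may specify a robust one. This stands in part, and it is why the point is conditional. It does not remove the point: the article itself permits a mixed-effects Poisson model for yes/no data and names only a device that cannot reduce variance. Followed as written with default standard errors, that option gives wrong intervals.

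Second, the binomial model is listed first, and a log-binomial model that converges has the right variance. This also stands. Such models can be hard to fit when risks are close to 1, but nothing in the article shows that this would happen here.

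Three stronger readings are tempting and are not supported:
- **That intervals for viral suppression will be about 1.4 to 3 times too wide.** Those factors come from the formula that ignores clustering, at p of 0.50 and 0.89. With the plan's ICC the same prevalences give 1.24 and 2.64. As no suppression rate is given, no single factor can be assigned to that outcome.
- **That a real benefit would be missed.** It could be. At 40% v 55% the Poisson analysis still detects the difference 59% of the time.
- **That all three binary outcomes are affected.** Diarrhoea, if reported by about 20% or fewer, is essentially untouched.

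**Conclusion.** The point holds in conditional form and is minor. If the Poisson option is used with default standard errors, risk-ratio intervals for common outcomes are too wide: by about 1.24 times at 50% prevalence, 1.6 at 70%, 2.0 at 80% and 2.8 at 90%, with no excess at about 20% or less. These figures rest on assumed prevalences, on the ICC of 0.05 carrying over from the BSID-III calculation to binary outcomes, on 28 clusters per arm, and on leaving out the counsellor effect.

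The error is conservative: it loses precision and power and does not produce false positives. The co-primary outcomes are unaffected.

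**What to change.** In *Statistical methods for primary and secondary outcomes {20a}*, add that if a Poisson model is fitted to a binary outcome, standard errors will be robust, clustered on geospatial cluster, with a small-sample correction. Alternatively, replace the Poisson option with mixed-effects logistic regression and marginal standardisation to a risk ratio. If the SAP already provides for either, it is enough to confirm that and align the wording.

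The cost is one sentence and one extra analysis step. Robust standard errors are slightly less stable with 48–60 clusters, which is the reason for the small-sample correction.

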##### Personnel—recruitment, training, and supervision

The ESoC is delivered by an experienced ESoC caller who has at least 2 years of counselling experience, including working with women and children, and providing HIV counselling. The ESoC caller attends a 4-week intensive training workshop followed by a mock telephone call competency assessment and intensive supervision over the first 2 months. Periodic refresher training is provided. The training includes the identification of risk situations, including suicidal ideation. The ESoC caller receives weekly supervision and debriefing with a trained counselling supervisor, to support and facilitate referrals in risk cases and in managing the logistical aspects of the ESoC. The caller contacts the ESoC supervisor between supervision sessions if issues of concern or uncertainty arise.

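### The primary model nests counsellor within geospatial cluster, but the planned 4 counsellors must span about 28 intervention clusters, so the standard error is too small if counsellors differ

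*Protocol article*

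**What the plan says.** The article's section on statistical methods for primary and secondary outcomes {20a} sets the random-effects structure: "the geospatial cluster and counsellor identifier will be fitted as random effects, with counsellor nested within the geospatial cluster". It promises to report an intra-class correlation for each of the two levels. It also warns that ignoring dependence among women understates the standard error.

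Sample size {14} assumes "28 clusters per arm with an intra-cluster correlation coefficient (ICC) of 0.05" and, for the intervention arm, "4 lay counsellors with an ICC of 0.05". The recruitment target is given as "264 per arm, 48–60 geospatial clusters, 9–11 women per cluster", which is 24–30 clusters per arm. Intervention description {11a} gives each woman one counsellor for all ten sessions and the booster. Nothing in the article says that a counsellor works in one cluster only, and no other random-effects structure is described.

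**The concern.** Counsellor can be nested within cluster only if each counsellor belongs to a single cluster. Four counsellors over 24–30 intervention clusters rule that out: either clusters lie within counsellors, or the two factors cross.

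Under the nested coding, every counsellor-by-cluster combination gets its own independent effect, and women who share a counsellor but live in different clusters are treated as uncorrelated. The counsellor variance is then averaged over 28 or more units when only 4 exist. The stakes are a standard error that is too small for the primary comparison, and a published counsellor ICC that does not measure variation between counsellors.

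**Working it through.** **Inputs** (Sample size {14}): SD 15, so variance 225; 198 women per arm analysed; 28 clusters per arm; geospatial ICC 0.05; 4 counsellors in the intervention arm; counsellor ICC 0.05; difference 6 points; two-sided 5%.

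**Quantities used throughout**
- Women per cluster: 198/28 = 7.07. Women per counsellor: 198/4 = 49.5.
- Variance of an arm mean without clustering: 225/198 = 1.136.
- Control arm, geospatial clustering only: 1 + 6.07 × 0.05 = 1.304; variance 1.136 × 1.304 = 1.481.

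**The plan's own figures**
- The total reproduces: 396/0.75 = 528.
- Power with geospatial clustering only: SE = √(2 × 1.481) = 1.72; 6/1.72 − 1.96 = 1.53; power 93.6%.
- Power of over 90% is therefore reached when the counsellor effect is left out. As shown below, it is also reached when the effect is treated as independent in each cluster, but not with 4 shared counsellors.

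**Standard error with 4 counsellors shared across clusters**
- Intervention design effect: 1 + 6.07 × 0.05 + 48.5 × 0.05 = 3.729; variance 1.136 × 3.729 = 4.237.
- Variance of the difference: 4.237 + 1.481 = 5.718; SE = 2.39.
- Power for 6 points: 6/2.391 − 1.96 = 0.549, giving 70.9%. For 24–30 clusters per arm it is 69.9–71.3%.

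**Standard error under nesting, one counsellor per cluster**
- Intervention design effect: 1 + 6.07 × (0.05 + 0.05) = 1.607; variance 1.826.
- Variance of the difference: 1.826 + 1.481 = 3.308; SE = 1.82.
- Power would appear to be 91.0%.
- Ratio 1.82/2.39 = 0.76, so the standard error is 24% too small.
- Type I error: 2 × [1 − Φ(1.96 × 0.76)] = 13.6%.

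If all 4 counsellors work within each cluster, the nested SE is 1.73, apparent power 93.3% and type I error 15.5%.

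**Dependence on the counsellor ICC (analytic, 4 counsellors)**

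| Counsellor ICC | One counsellor per cluster | Counsellors mixed within clusters |
|---|---|---|
| 0 | 5.0% | 5.0% |
| 0.01 | 6.9% | 7.2% |
| 0.02 | 8.7% | 9.3% |
| 0.03 | 10.4% | 11.5% |
| 0.05 | 13.6% | 15.5% |

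**Dependence on staffing** (assumed numbers, ICC 0.05, one counsellor per cluster): 10.3% with 6 counsellors, 8.6% with 8, 6.9% with 12.

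**Simulation** (zero average effect, 28 clusters and 198 women per arm, 4 counsellors, maximum likelihood with a Wald z test, 1,200 runs per setting, simulation error about 1 percentage point)
- ICC 0.05, nested model: 15.9% with one counsellor per cluster, 17.5% with counsellors mixed.
- ICC 0.05, shared-counsellor model on the same data: 10.7% and 11.6%.
- ICC 0.02, nested model: 11.3% in both layouts.

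A larger run (40,000 data sets, 7 women per cluster, each counsellor covering 7 clusters, ICC 0.05) gave 15.3% for the nested model. With the correct structure it gave 10.1% with maximum likelihood and z, 8.1% with REML and z, and 5.9% with Satterthwaite degrees of freedom.

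**The case against.** The strongest reply is that the figure rests on planning values. That stands: neither the counsellor ICC of 0.05 nor the number of counsellors actually employed is reported as observed. A reader might infer that the trial's false-positive rate is 15%. The documents support only a conditional statement, which shrinks with a smaller ICC or more counsellors.

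A second reply is that not all of the simulated 15–18% comes from nesting. That also stands. With the correct structure, maximum likelihood and z still give about 10–11%, because there are only 4 counsellors. The analytic 13.6% takes the variances as known and so isolates the nesting.

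Third, a false positive here means that the average effect is zero while counsellors differ. If the intervention did nothing under any counsellor, there would be no counsellor variance and no excess. Fitting counsellor as random implies the wider inference, and the article's Discussion looks to roll-out beyond these counsellors.

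Three further readings are tempting but not supported:
- **That the plan prescribes z intervals.** It does not. "Mixed-effects models with maximum-likelihood estimation" appears where the article explains how incomplete repeated measures are kept, and the choice of degrees of freedom is commonly left to the SAP.
- **That one control-arm caller is fully confounded with arm.** "The ESoC is delivered by an experienced ESoC caller" is singular, but the ESoC fidelity paragraph speaks of callers in the plural. A single caller would in any case be a design feature that the nesting clause neither creates nor cures.
- **That the model cannot be fitted.** Software will fit it; the fault is that it does not match the design.

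The SAP may specify something else, but it would then contradict the structure published here.

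**Conclusion.** The clause is wrong as written, because it contradicts the staffing in the same article. With 4 counsellors, a counsellor ICC of 0.05, SD 15, 198 women per arm and counsellors regarded as random, the BSID-III standard error is about 1.82 where it should be about 2.39. Type I error is about 14% analytically and about 15–18% in simulation with maximum likelihood and an assumed z test. It is about 7% at an ICC of 0.01 and 9–11% at 0.02, and nesting adds nothing at 0.

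A reader might infer that the same size has been shown for EPDS. It has not. The article applies the same clustering assumptions to EPDS, so the direction should carry over, but its planned analysis is a repeated-measures model that was not evaluated here.

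**What to change.** Replace the nesting clause in {20a}. Fit a random intercept for geospatial cluster in both arms, and a separate counsellor random effect that is crossed with or above cluster and applies in the intervention arm only. State REML with Satterthwaite or Kenward–Roger degrees of freedom, because correcting the structure alone leaves about 10–11% with maximum likelihood and z. REML still keeps women with incomplete repeated measures. Report the counsellor ICC from this model.

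The degrees-of-freedom method needs care with so few counsellors. Satterthwaite gave about 6%, whereas a fixed t reference on 3 degrees of freedom gave 1.7% and 1.2% in the two layouts, which is conservative.

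The direct cost is one sentence and the model code. Intervals will be wider. The power statement in {14} should be restated: these inputs give about 71% for 6 points with 396 women. Trial status reports recruitment closed in July 2021, so the loss of power can be disclosed but not made up by recruiting more women.

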Rumination	Brief Rumination Response Scale [61]	Baseline, end of pregnancy, 12 weeks, 12 and 24 months
Maternal recognition of infant faces and sounds	Stimuli task	Baseline, 12 months

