#### Methods in analysis to handle protocol non-adherence and any statistical methods to handle missing data {20c}

Women with outcome data will be analysed in the groups to which they are randomly assigned, regardless of deviation from the protocol or treatment received (modified ITT population). Women whose infant died during the trial will also be included unless they withdrew consent to participate further in the trial.

The number and percentage of individuals missing data for outcome measurements that are based on summing items to give overall scores (e.g. EPDS, GAD-7, and subscales of the PSI/SF and CBCL) will be described. Missing items will be imputed if ≤ 20% are missing using the median score of completed scale items unless alternative guidance is provided in the scoring manual.

A multiple imputation analysis will be performed for the primary infant and maternal outcome if attrition exceeds 5%. The multiple imputation model will include baseline characteristics and outcome measures collected before the missing assessment, which are associated with missing status.

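### The primary model's covariates are chosen from differences seen in the trial's own data, under a rule with no criterion and only half limited to baseline variables

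*Protocol article*

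**What the plan says.** Section {20a} of the protocol article names the endpoints: "The primary inference will be based on the BSID-III cognitive score at 24 months and the EPDS at 12 months". Both are analysed by mixed-effects linear regression. The EPDS goes into a repeated-measures model with its baseline, end-of-pregnancy, 12-month and 24-month scores.

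Covariates enter by two rules, given in one sentence: "adjusting for important baseline differences between randomised groups, any differences between participants followed up to 24 months and those lost to follow-up". The second rule reads in full that "any differences between participants followed up to 24 months and those lost to follow-up will be adjusted for in the final models". Unadjusted models are also fitted, but "the primary inference will be based on the adjusted model which provides unbiased estimates if the outcome data is missing at random".

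Two neighbouring sections bear on this:

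- Section {20b} names maternal education, socio-economic class, severity of depression at entry and infant sex as known correlates of infant cognitive development. It uses them only for subgroup tests.
- Section {20c} plans multiple imputation of the primary outcomes if attrition exceeds 5%. There, "The multiple imputation model will include baseline characteristics and outcome measures collected before the missing assessment", where these are associated with missingness.

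**The concern.** Neither rule can be applied until trial data are in hand. The first needs baseline data by arm, and the second needs to know who was retained to 24 months. Three problems follow.

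- **Wrong selection criterion.** In a randomised trial, a chance difference between arms says nothing about whether a variable predicts outcome. A strong predictor that happens to be balanced is left out, and a weak one that happens to differ is put in.
- **Undefined discretion.** With no criterion for *important*, two competent analysts could fit different primary models to the same data.
- **Open scope.** The first rule says baseline and the second does not. If a variable measured after allocation differed between retained and lost women, the wording would let it into the outcome model. If the intervention had changed that variable, the model would no longer estimate the total effect of treatment.

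**Working it through.** **1. The text.** The first clause is restricted to baseline; the second covers any difference and carries no such restriction. Section {20c} gives earlier outcome measures a place in the imputation model, but it does not say what may enter the outcome model of {20a}. Variables that could qualify after allocation include EPDS at the end of pregnancy and 12 weeks (Table 4), and rumination and family support, which Table 3 lists as mediators measured at "Baseline, end of pregnancy, 12 weeks, 12 and 24 months". Both mediators therefore also have a baseline value, for which adjustment would be legitimate.

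**2. Will the second rule be triggered?** Sample size {14} gives 396 evaluable women and up to 25% attrition. 396 / (1 − 0.25) = 528, which reproduces the plan's figure. At that attrition, 528 − 396 = 132 women are lost, so retained and lost women would be compared as 396 against 132. Some difference is likely to appear.

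**3. Precision forgone** (assumed correlation r between covariate and outcome; individual-level calculation, clustering ignored).

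- SE ratio, always adjusted to unadjusted: √(1 − r²).
- r = 0.5: √0.75 = 0.866, a cut of about 13%. Simulation with 198 per arm, in SD units: 0.101 unadjusted, 0.088 adjusted.
- r = 0.3: √0.91 = 0.954, a cut of about 5%. Simulation: 0.102 and 0.097.
- If imbalance were judged by p < 0.05 (an assumption; the plan gives no threshold), a given baseline covariate would enter in about 1 trial in 20, so the gain is usually lost.

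**4. Type I error** (null simulation: N = 396, 8 baseline covariates jointly explaining an assumed 30% or 50% of outcome variance, 3,000 runs, clustering ignored).

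| Model | R² = 0.3 | R² = 0.5 |
|---|---|---|
| Fixed set of all 8 | 4.4% | 4.8% |
| Adjust if imbalance p < 0.05 | 3.8% | 3.7% |
| Adjust if p < 0.10 | 3.1% | 3.1% |
| Adjust if p < 0.20 | 3.2% | 2.5% |
| Smallest p of these four and the unadjusted model | 7.7% | 8.7% |

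Monte Carlo error near 5% is about √(0.05 × 0.95 / 3000) = 0.4 percentage points. A mechanical imbalance rule is conservative. Only free choice among models after seeing their results inflates the error.

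**5. Over-adjustment, if a post-baseline variable were entered.** Take EPDS as the variable and BSID-III as the outcome. The planned BSID-III effect is 6 points and the EPDS difference is 2 points (both from {14}). Assume a slope of 0.3 to 1.5 BSID-III points per EPDS point.

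- Remaining effect = 6 − 2 × slope, so 5.4 points at slope 0.3 and 3.0 points at slope 1.5. Between 10% and 50% of the effect is adjusted away.
- Geospatial clustering only: 396 / 56 = 7.07 women per cluster; design effect 1 + 6.07 × 0.05 = 1.304; SE = 15 × √(2 × 1.304 / 198) = 1.72 points.
- Power at 6 points: Φ(6/1.72 − 1.96) = 93.6%. At 5.4 points it is 88.0% and at 3.0 points 41.4%.
- These power figures hold the SE at 1.72. A covariate that predicts outcome would also reduce the SE, so they overstate the loss in power. The shrinkage of the estimate does not depend on this.

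**The case against.** The strongest defence is that the rule has a purpose. Adjusting for predictors of drop-out is meant to support a missing-at-random analysis with up to 25% attrition planned, and a list of covariates is ordinary SAP content. The absence of a list is indeed no finding. But the article does not leave the matter open: it states a selection rule for the primary model, and the rule itself is the weakness.

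Several stronger readings are tempting and are not supported.

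- **That the plan will adjust for mediators or other post-randomisation variables.** The sentence opens with baseline differences, and comparing the baseline profile of retained and lost women is its natural sense. Section {20c} gives earlier outcomes a separate place. The wording permits such covariates and no more, so the shrinkage in step 5 is conditional on a reading that the authors may not intend.
- **That the rule inflates type I error.** Step 4 shows the opposite for a rule applied mechanically.
- **That covariates are chosen after unblinding or after seeing results.** The timing is not stated. Retained and lost women can be compared with arms pooled, and baseline balance can be examined without outcomes.
- **That 24-month retention is the wrong basis for the 12-month EPDS.** It is an imperfect proxy for missingness at 12 months, but the EPDS model includes the 24-month score, so the point is minor.
- **That both outcomes lose precision equally.** The EPDS model already contains the baseline EPDS, whatever the balance between arms.

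**Conclusion.** The point holds in a limited form. Section {20a} ties the primary inference to covariates selected from observed differences, with no criterion for the first rule and no baseline restriction on the second. That leaves avoidable discretion in the primary analysis. It also forgoes precision, mainly for BSID-III, even though {20b} already names factors known to be associated with that outcome.

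The size is moderate: about 13% of the standard error for one covariate with an assumed correlation of 0.5, and about 5% at 0.3. Over-adjustment of BSID-III could remove 0.6 to 3.0 of the planned 6 points, but only if a post-baseline variable such as EPDS is entered, and on assumed slopes. None of the correlations, slopes or R² values comes from the documents. The change should be made; nothing here shows that the planned analysis is invalid.

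**What to change.** Replace the rule in {20a} with a fixed set of baseline covariates, named before any comparison by arm.

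- **Both outcomes:** for example maternal education, paid employment, maternal age and gestation at enrolment.
- **BSID-III only:** add screening EPDS and infant sex. Infant sex is recorded after birth but settled before allocation, so treatment cannot change it.
- **EPDS model:** do not add screening EPDS as a separate covariate. The repeated-measures model already includes the baseline score, and Table 4 shows screening as the only EPDS before allocation, so the same measurement would be used twice.
- **Drop-out:** limit any further adjustment for predictors of drop-out to baseline variables. Keep post-baseline predictors in the repeated-measures likelihood or in the imputation model of {20c}.
- **Imbalance-driven adjustment:** report it only as a sensitivity analysis.

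The cost is wording in the protocol or SAP. The variables are collected already or follow from eligibility screening and the planned subgroups. Recruitment closed in July 2021, so when the article appeared in December 2021 the 24-month outcomes of the last women enrolled were still to come.
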